#### Relaxation training

Participants randomised to the control treatment receive a 5-session relaxation training program over a period of 10 weeks, as detailed in Table 2. Participants receive training in progressive and passive muscle relaxation, meditative relaxation, visualisation and “quick relaxation” techniques, with regular home-based practice and a CD for practice outside sessions. The aim of the control condition is to provide an equivalent amount of therapist contact to Conquer Fear, to control for non-specific therapeutic factors (e.g. therapeutic alliance and support), in a treatment package with face validity so that patients are not aware they are in the control condition. Relaxation therapy may have some beneficial effects itself.

**Table 2 T2:** Detailed content for the relaxation training intervention

**Session**	**Content**	**Home based practice**
1	• Assess FCR;	Practice active PMR daily for 25 minutes
	• Explain concept of stress, how it can be adaptive when it becomes a problem and how it can be managed through relaxation;	
	• Introduce different stress management techniques;	
	• Practice active progressive muscle relation (PMR);	
2	• Review active PMR and its impact on stress levels;	Practice passive PMR daily for 25 minutes
	• Identify and resolve issues of practicing active PMR;	
	• Introduce passive PMR;	
	• Practice passive PMR;	
3	• Review passive PMR and its impact on stress levels;	Incorporate meditative relaxation into passive PMR practice for 25 minutes daily
	• Identify and resolve issues of practicing passive PMR;	
	• Introduce meditative relaxation;	
	• Practice meditative relaxation.	
4	• Review meditative relaxation and its impact on stress levels;	Incorporate visualisation into passive PMR practice for 25 minutes daily
	• Identify and resolve issues of practicing meditative relaxation;	
	• Introduce visualisation as a way of shortcutting the stress response;	
	• Practice visualisation.	
5	• Review visualisation and its impact on stress levels;	
	• Identify and resolve issues of practicing visualisation;	
	• Introduce quick relaxation techniques;	
	• Practice quick relaxation;	
	• Review skills learnt and progress made;	
	• Develop plan for future practice of relaxation techniques.	

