#### Potential covariates

Clinical and demographic information will include age, time since diagnosis, marital status, education, parity, stage of disease, treatment received (both medical and psychological) and current treatment (e.g. anti-depressants (if any)). In addition individual level of perceived risk of cancer recurrence will be assessed as this may influence firstly level of FCR prior to treatment and also treatment efficacy. Other potential covariates related to treatment are therapeutic alliance and treatment expectancy and credibility. Therapeutic alliance, which has consistently been shown to be associated with treatment outcome [54], will be assessed using the 12-item Working Alliance Inventory short-form revised (WAI-SR) [55]. The WAI-SR assesses the agreement on goal, the agreement on tasks that achieve the goal, and bond between patient and therapist. Treatment expectancy, which has been shown to predict treatment outcomes in a variety of contexts [56], will be measured using the 6-item Credibility/Expectancy Questionnaire [57].

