#### Statistical analysis

Analyses will be by intention-to-treat. Linear mixed models will be used to account for the hierarchical, non-independent nature of the data: repeated measures on patients nested within therapist. A saturated time x treatment model with unstructured covariance structure will be used to guard against misspecification of the model. Random effects of patient and therapist will be used. The primary analysis will be the comparison at the each of the 3 post-baseline (post-treatment) time points of the two arms using a contrast within this mixed model. Overall pattern of change will be assessed by testing the treatment by time interaction. Adjusted analysis, including using baseline FCRI, sex, age, time since diagnosis, cancer type, perceived risk, treatment expectancy and therapeutic alliance will also be investigated. Variables will be included in the model if they have a Kendall’s Tau correlation higher than 0.1 with FCRI. Mixed models yield unbiased estimates for data which are missing completely at random and at random [62], however, if the amount of missing data for the primary outcome is greater than 20%, sensitivity analyses will be performed by multiply imputing the missing data, and adding and subtracting clinically plausible amounts from the imputed values. These new datasets will be re-analysed, to see how conclusions change.

Secondary outcomes (QoL, distress, unmet information needs) will be analysed in a similar way to the primary outcome. Treatment satisfaction and therapist training evaluation will be described with descriptive statistics. To see if colorectal and breast cancer patients responded differently to the treatment, we will test the interaction cancer type x treatment x time. Predictors of FCR, distress and QoL at baseline will be explored using multiple linear regression. The relationship between Metacognition and FCR will examined using 1) regression to see if there is a relationship at baseline in the entire sample and then 2) using mediation techniques following the methods of Baron and Kenny [63] in the treatment group only, immediately post baseline (time 1). The CAR-Q will be compared with the FCRI using psychometric techniques.

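### The supporting adjusted analysis lists therapeutic alliance, which forms only after allocation, and treatment expectancy, whose timing is not stated, as candidate adjusters of the arm comparison

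*Protocol article*

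**What the plan says.** Under Statistical analysis, the primary analysis is a mixed-model contrast of the two arms at each of the three post-treatment time points, by intention-to-treat. An adjusted analysis follows. Its candidate covariates are age, sex, cancer type, time since diagnosis and the baseline FCRI score, and the list ends: "perceived risk, treatment expectancy and therapeutic alliance will also be investigated". A candidate enters the model if it has a Kendall's "Tau correlation higher than 0.1 with FCRI".

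Under Potential covariates, two of these are set apart from the clinical and demographic items: "Other potential covariates related to treatment are therapeutic alliance and treatment expectancy and credibility". The alliance scale (WAI-SR) covers agreement on the goal, "the agreement on tasks that achieve the goal, and bond between patient and therapist". Both measures are presented as related to outcome: "Therapeutic alliance, which has consistently been shown to be associated with treatment outcome" and "Treatment expectancy, which has been shown to predict treatment outcomes in a variety of contexts". No time point is given for either.

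Under Randomisation, the therapist receives the patient's contact details together with the allocation, after the envelope has been opened. Under Relaxation training, the control arm supplies an equal amount of therapist contact, "to control for non-specific therapeutic factors (e.g. therapeutic alliance and support").

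**The concern.** An adjusted treatment comparison keeps its randomised meaning when the covariates are fixed before allocation. A covariate that the assigned arm can change is different. Conditioning on it compares patients who reached the same level of alliance under two different therapies, and randomisation does not make those patients comparable. The adjusted difference may leave out an effect that runs through alliance. It may also pick up bias from unmeasured causes shared by alliance and fear of recurrence.

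The arms give alliance room to differ. Two of its three components are agreement on goals and on tasks, and Tables 1 and 2 of the article set different goals and tasks for the two programmes.

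What is at stake is the reading of a supporting analysis. If adjusted and primary results disagree, the reader could not tell whether prognostic adjustment or post-allocation conditioning was the cause. The article says that secondary outcomes will be analysed in a similar way, so the same ambiguity may carry over to them.

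**Working it through.** **1. Timing, from the text.**
- Alliance: the scale rates goals, tasks and bond with the therapist. The therapist receives the patient's details only with the allocation, so alliance in the study therapy is necessarily post-randomisation.
- Expectancy and credibility: described as related to treatment, with no time point. A questionnaire is completed before randomisation (Outcomes), and nothing says whether expectancy is in it. Its status is open.

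**2. Does the entry rule keep alliance out?** It selects on association with FCRI and not on time of measurement. Under bivariate normality a tau of 0.1 corresponds to r = sin(π/2 × 0.1) = 0.156, which is a low bar for a variable that the article calls consistently associated with outcome. I read the threshold as an absolute value, since higher alliance would be expected to go with lower FCRI.

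**3. The planning figures.** Effect 14.5, SD 29, so 14.5 / 29 = 0.5 SD. With 90% power and two-sided α = 0.05, n = 84.06 per arm. The design effect with 13 × 0.7 = 9.1 analysed patients per therapist is 1 + (9.1 − 1) × 0.01 = 1.081. Then 2 × 84.06 × 1.081 / 0.7 = 259.6, which matches the stated 260. The point here does not depend on the sample size; 14.5 and 29 serve only as the scale.

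**4. Size of the shift.** In a linear model with one such covariate,

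adjusted effect = total effect − (within-arm slope of FCRI on covariate) × (arm difference in covariate).

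With the covariate in SD units, the size of the shift is a × b × 29 points, where a is the arm difference in SD and b the absolute standardised slope. The documents give neither, so both are assumed:

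| a | b | shift in SD | shift in points | share of 14.5 |
|---|---|---|---|---|
| 0 | any | 0 | 0 | 0% |
| 0.2 | 0.2 | 0.04 | 1.16 | 8% |
| 0.3 | 0.3 | 0.09 | 2.61 | 18% |
| 0.5 | 0.4 | 0.20 | 5.80 | 40% |

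When higher alliance goes with lower FCRI, the shift shrinks the apparent benefit if alliance is higher under Conquer Fear and enlarges it if alliance is higher under relaxation. For example, with a = b = 0.3 the adjusted benefit is 14.5 − 2.61 = 11.89 points in the first case and 14.5 + 2.61 = 17.11 in the second.

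**5. Is the adjusted figure at least a clean direct effect?** Not necessarily. In a simulation of 1,000,000 patients, alliance had no causal effect on FCRI, and an unmeasured factor drove both. The true effect of assignment was 14.5 points, none of it through alliance.

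| a | within-arm correlation (absolute) | formula | simulated adjusted effect |
|---|---|---|---|
| 0.3 | 0.3 | 11.89 | 11.97 |
| 0.3 | 0.5 | 10.15 | 10.07 |
| 0.5 | 0.3 | 10.15 | 10.18 |
| 0.5 | 0.5 | 7.25 | 7.20 |

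The shift is nearly the same as the formula gives, although nothing was mediated. From the adjusted model alone, mediation and shared-cause bias cannot be told apart.

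**The case against.** The strongest reply is that the trial's main result is untouched. The primary contrast does not list these covariates and will be reported whatever the adjusted model shows. That stands. A reader might infer that the efficacy result itself is biased; the article does not support that.

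A reader might also infer that both variables will certainly be in the model. Entry depends on the tau rule. It is likely, given what the article says about both measures and outcome, but it is not settled.

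Third, a reader might take expectancy as post-allocation because it is called related to treatment. The article does not say when it is measured, and such timing is often left to a full protocol. If it is measured before randomisation, adjusting for it is harmless. The firm part of the point is alliance.

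Fourth, the design works towards balance. Therapists are trained in both manuals, randomisation is stratified by therapist, both programmes have five sessions over 10 weeks, and participants do not know which intervention is under evaluation. If alliance ends up equal, the shift is near zero. This lowers the expected size but is no reason to keep the covariate: with balance there is no arm difference to adjust away, and without balance the adjusted estimate answers a different question.

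Finally, the article does not state what the adjusted analysis is meant to estimate. That is true, but it sits among the efficacy analyses under an intention-to-treat heading and is not labelled as a process analysis. The only mediation analysis named concerns metacognitions, in the treatment group only.

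**Conclusion.** The point holds for the supporting adjusted analysis. As written, the plan allows a variable that can arise only after allocation to adjust the arm comparison, under an entry rule that does not exclude it. If alliance enters and differs by arm, the adjusted difference is not the effect of assignment. The conclusion is firm for alliance and conditional on timing for expectancy.

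Size and direction cannot be fixed from the documents. Under the assumed arm differences of 0.2 to 0.5 SD and slopes of 0.2 to 0.4, the shift is about 1.2 to 5.8 FCRI points, 8 to 40% of the planned 14.5, in either direction. With balanced alliance it is near zero. Reading that range as a share of the effect that will be removed would go too far, because it leaves out both zero and a shift in the other direction.

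This should be fixed, but it is not a fault in the primary analysis or the sample size.

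**What to change.** Restrict the adjusted efficacy model to covariates measured before randomisation. Remove therapeutic alliance from its list. State when expectancy and credibility are measured, and keep them only if that is before randomisation. Apply the tau rule only within the pre-randomisation set.

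Report alliance, and any expectancy measured after allocation, by arm, and use them only in a separately labelled exploratory process or mediation analysis. Use the same restricted list wherever secondary outcomes are adjusted.

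The cost is a line or two of wording. All measures are still collected and used, and neither the sample size nor the primary contrast changes.

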#### Primary outcome

Fear of Cancer Recurrence is assessed using the 42-item FCRI [39], the most comprehensive multi-dimensional scale of FCR available, and suitable for patients with mixed cancer diagnoses. It has been found to be internally consistent (Chronbach’s α=0.75 to 0.91 across subscales) and stable over a two-week interval (ρ = 0.58 to 0.83 across subscales), and has a robust factor structure. The FCRI has convergent validity with other standardised measures of FCR (ρ = 0.66 to 0.77) and discriminant validity with QOL amongst a large sample (n = 600) of Canadian cancer patients with mixed tumours [39]. Respondents rate the degree to which symptoms or issues affect them on a Likert scale ranging from 0 (‘not at all’ or ‘never’) to 4 (‘a great deal’ or ‘all the time’). Higher scores indicate higher FCR.

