#### Sample size

This is a longitudinal randomised controlled trial, with one baseline measure and 3 post-intervention measures. The primary outcome is the Fear of Cancer Recurrence Inventory, a 42 item scale with a possible range of 168.

We based our sample size calculation on 90% power, a two-sided α = 0.05 t-test, dropout of 30%, a difference between groups of 14.5, and a standard deviation of 29 [39] (a standardised effect size of 0.5). The sample size calculations should account for the clustering of outcomes by therapist, and although there is no published intra-cluster correlation (ICC) for the FCRI, we took guidance from two large reviews on ICCs in similar contexts [59,60] and used an ICC of 0.01. Assuming a total of 20 therapists, and following Donner and Klar, [60,61] the required sample size is 13 patients per therapist, for a total of 260 patients. If dropout is lower, for example, 20% then this sample size allows for a larger intra-cluster correlation or a small detectable difference. This sample size also gives 90% power to detect a difference of 0.5SD between the groups in each of the secondary outcomes. The value includes attrition of 30%, however, we expect attrition to be lower, since patients with FCR report a high level of need for help, and we experienced low attrition when piloting the intervention.

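### The supplementary adjusted analysis chooses its covariates by their observed correlation with FCRI instead of fixing them in advance, and the threshold omits the words absolute value (minor)

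*Protocol article*

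**What the plan says.** The Statistical analysis section of the Protocol article defines the primary analysis first: "The primary analysis will be the comparison at the each of the 3 post-baseline (post-treatment) time points of the two arms using a contrast within" the mixed model. No covariate filter is attached to it.

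A further analysis follows: "Adjusted analysis, including using baseline FCRI, sex, age, time since diagnosis, cancer type, perceived risk, treatment expectancy and therapeutic alliance will also be investigated". The next sentence sets the condition for entry, a Kendall's "Tau correlation higher than 0.1 with FCRI". It exempts none of the listed candidates, so baseline FCRI is subject to it as worded. It does not say whether the sign of tau counts or which of the four FCRI assessments is used.

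The Primary outcome section gives the direction of the scale: "Higher scores indicate higher FCR". A covariate that goes with less fear therefore has a negative tau. The article does not give the coding of sex or cancer type.

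**The concern.** Two features of the rule deserve attention.

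The first holds on any reading. The covariates are chosen by how strongly they correlate with the outcome in this trial's own data. An adjusted analysis is most useful when its model is fixed before outcomes are seen. Here covariates near the threshold enter or leave by sampling noise, and the model is unknown until the correlations have been computed.

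The second is wording. Tau runs from -1 to +1, and the rule does not mention absolute value. An analyst who applied it literally would drop every covariate that goes with lower FCRI. For a two-category covariate such as sex or cancer type, entry would turn on which category is coded 1.

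At stake are the precision and reproducibility of the adjusted estimate. The validity of the primary comparison is not in question.

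**Working it through.** **Number of patients.** The threshold of 0.1 has no derivation in the article, so there is no figure of that kind to reproduce. The planned size sets the sampling error of tau, and it does reproduce. The inputs, from the Sample size section, are "90% power, a two-sided α = 0.05 t-test, dropout of 30%, a difference between groups of 14.5", "a standard deviation of 29" and the statement that the planners "used an ICC of 0.01".

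- Per arm: 2 × (1.960 + 1.282)² × (29/14.5)² = 84.1, rounded up to 85, so 170 in total.
- Evaluable patients per therapist: 13 × 0.7 = 9.1. Design effect: 1 + (9.1 - 1) × 0.01 = 1.081.
- Total: 170 × 1.081 / 0.7 = 262.5, close to the stated 260 (20 therapists × 13).

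The correlation would rest on between 260 × 0.7 = 182 patients (follow-up with full dropout) and 260 (baseline, or no dropout). The time point is not stated, so both ends are shown.

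**Sampling error of tau.** The null standard error is √[2(2n + 5) / (9n(n - 1))].

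- n = 182: √(738 / 296,478) = 0.050.
- n = 260: √(1,050 / 606,060) = 0.042.

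**Chance of entry when the size of tau is used.** This is a normal approximation using the standard errors above. The true values of tau are assumed, because the article gives none.

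| True tau | Kept, n = 182 | Kept, n = 260 |
|---|---|---|
| 0 | 4.5% | 1.6% |
| 0.10 | about 50% | about 50% |
| 0.15 | about 84% | about 88% |

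Simulation agrees: 50% and 49% kept at a true tau of 0.10, and 16% and 12% dropped at 0.15.

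**What a dropped covariate costs.** For a bivariate normal pair, tau = (2/π) arcsin(r), so r = sin(π × tau / 2). With a covariate of correlation r in the model, the standard error of a simple arm comparison is multiplied by about √(1 - r²).

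- tau 0.10: r = 0.156, r² = 0.024, factor 0.988, a gain of about 1%.
- tau 0.15: r = 0.233, r² = 0.054, factor 0.972, a gain of about 3%.

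**What the literal, signed reading would do.** These are illustrations under assumed effect sizes.

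- r = -0.5, -0.4, -0.3 and -0.2 give tau = -0.33, -0.26, -0.19 and -0.13. All exceed 0.1 in size, and all fail a signed rule.
- With r = -0.4 and n = 260, 2,000 simulated trials kept the covariate 0% of the time under the signed rule and 100% under |tau| > 0.1. The precision forgone would be √(1 - 0.16) = 0.917, about 8% of the standard error.
- A binary covariate with a 0.5 SD difference in FCRI has tau-b of about ±0.20 (50:50 split), ±0.15 (20:80) or ±0.12 (10:90). The sign depends only on coding. Under |tau| > 0.1 all three population values pass under either coding.

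**The case against.** **The signed reading is not established.** A reader might infer that the rule deliberately discards strong negative predictors. The text does not say that: it neither specifies positive correlations nor excludes negative ones. A correlation above some value is ordinary shorthand for strength of association. The odd dependence on coding is itself a sign that magnitude was meant. The article is condensed, and a fuller document may already specify the absolute value. This objection stands. The 0% against 100% contrast shows what the literal wording would do and does not describe what the sponsor plans.

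**Half retention at the threshold is true by construction.** Any covariate lying exactly on a cut-off passes about half the time, and at tau 0.10 it explains only about 2.4% of the variance. Further away the rule is stable: at n = 260 pure noise enters 1.6% of the time, and a covariate with r = -0.4 always entered when magnitude was used. This also stands and keeps the point small. It does not remove it, because a covariate with a true tau of 0.15 is still dropped in roughly one trial in six to eight.

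**The rule is itself prespecified.** It names candidates, a statistic and a cut-off. It selects on correlation with FCRI, not on the treatment effect, and the Randomisation section has the biostatistician see only A and B. There is therefore little scope to steer the result. That is fair, but an algorithm fixed in advance still yields a model that depends on the outcome data, and a fixed list avoids this at little cost.

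**Baseline FCRI would be expected to pass anyway**, since it should correlate positively with later FCRI. That is likely, and it is also a reason not to make its inclusion conditional.

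**Conclusion.** The point holds as a minor one. On either reading, the adjusted model is selected from observed outcome correlations, and baseline FCRI is formally subject to the filter. If magnitude is meant, the cost is about 1% to 3% of the standard error for each wrongly dropped covariate with a true tau of 0.10 to 0.15, together with a model that cannot be stated beforehand. If the wording were applied literally, the loss could be larger, about 8% for an assumed r of -0.4, and entry of binary covariates would depend on coding. The documents support an ambiguity here, not a signed rule.

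A reader might also infer that the trial's main result is at risk. It is not: the primary contrasts are defined without the filter, and randomisation protects the arm comparison whichever baseline covariates enter.

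The figures rest on 182 to 260 patients, on normal approximations, and on assumed correlations, effect sizes and category splits that the article does not supply.

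**What to change.** Delete the tau filter. State that the adjusted analysis includes baseline FCRI, sex, age, time since diagnosis, cancer type and baseline perceived risk, whatever their observed correlation with FCRI. Therapeutic alliance is left off this list because it can be rated only once therapy has begun. Treatment expectancy is left off because the article does not say when it is measured.

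If a filter is kept, write |tau| > 0.1, name the FCRI time point, compute tau on data pooled over arms, and exempt baseline FCRI.

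The cost is one sentence and, with one term per covariate, about six degrees of freedom from roughly 180 to 260 patients (6/182 = 3.3%; 6/260 = 2.3%). No new data are needed, since all six variables are already listed for the adjusted analysis.

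### The only analysis that departs from missing at random runs only if more than 20% of the primary outcome is missing, so it may be skipped where a moderate effect could still be fragile

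*Protocol article*

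**What the plan says.** The primary analysis (Protocol article, Statistical analysis) is a linear mixed model with a saturated time-by-treatment mean. Its target is the "comparison at the each of the 3 post-baseline (post-treatment) time points of the two arms using a contrast within this mixed model". The model is justified for incomplete data by the statement that "Mixed models yield unbiased estimates for data which are missing completely at random and at random".

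The one analysis described that relaxes this assumption is conditional: "if the amount of missing data for the primary outcome is greater than 20%, sensitivity analyses will be performed". It consists of multiple imputation followed by "adding and subtracting clinically plausible amounts from the imputed values", and its purpose is given as "These new datasets will be re-analysed, to see how conclusions change".

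The Sample size section uses "90% power, a two-sided α = 0.05 t-test, dropout of 30%, a difference between groups of 14.5", with a standard deviation of 29, an ICC of 0.01, 20 therapists and 13 patients per therapist, 260 in all. On attrition it says "The value includes attrition of 30%, however, we expect attrition to be lower", and it discusses 20% as an example of a lower rate. The Pilot study section reports full retention, in 8 participants.

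**The concern.** A threshold on the quantity of missing data is being used to decide whether an assumption about its mechanism is examined. These are different things. Outcomes can be 15% missing and strongly informative, or 35% missing and harmless. For a given departure from MAR, the bias grows in proportion to the fraction missing; nothing changes in kind at 20%.

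The gate could well stay closed, because the protocol's own expectation is attrition below the planned 30%, with 20% as its example, and the rule requires more than 20%. The primary result would then be reported with no examination of whether non-responders in one arm fare differently from what the model predicts. If patients without an outcome in the Conquer Fear arm had higher fear scores than MAR implies, the estimated benefit would be too large.

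A second, lesser matter concerns the form of the analysis. The article does not say whether the amounts added or subtracted are the same in both arms. That matters because a common shift largely cancels in the arm difference when missingness is similar, whereas a shift in one arm does not.

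**Working it through.** **Inputs from the Protocol article, Sample size:** difference 14.5, SD 29, two-sided alpha 0.05, power 90%, ICC 0.01, 20 therapists, 13 patients each, N = 260, planned dropout 30%, example dropout 20%. **From Statistical analysis:** trigger above 20%. **Assumed for illustration:** equal allocation (130 per arm), the missing fractions by arm, shift sizes, and an observed difference of 10 points.

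**Step 1. Reproduce the plan's sample size.**
- Per arm, normal approximation: 2 × [29 × (1.960 + 1.282) / 14.5]² = 84.06.
- Evaluable patients per therapist: 13 × 0.7 = 9.1. Design effect: 1 + (9.1 − 1) × 0.01 = 1.081.
- Total: 2 × 84.06 × 1.081 / 0.7 = 259.6, which matches 260. The sample size is not in question.

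**Step 2. Does the gate open at the plan's own example?** At 20% dropout, 0.20 × 260 = 52 patients could lack the outcome. Twenty per cent is not greater than 20%, so the analysis is not run. At the planned 30% it would run.

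**Step 3. Effect of a shift on the contrast.** Let pT and pC be the fractions imputed in the Conquer Fear and relaxation arms at a visit, and dT and dC the shifts. In a saturated model on completed data, the arm difference changes by about pT·dT − pC·dC.

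| Missing (T / C) | Shift 14.5 in Conquer Fear only | Same 14.5 shift in both arms |
|---|---|---|
| 20% / 20% | 0.20 × 14.5 = 2.9 | 0 |
| 30% / 30% | 0.30 × 14.5 = 4.35 | 0 |
| 25% / 15% | 0.25 × 14.5 = 3.625 | 0.10 × 14.5 = 1.45 |
| 30% / 10% | 0.30 × 14.5 = 4.35 | 0.20 × 14.5 = 2.9 |

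A simulation with 26 of 130 missing per arm agreed: the mean difference was −9.91 without a shift, −9.91 with a common 14.5-point shift, and −7.01 with the shift in the Conquer Fear arm only.

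**Step 4. How much shift overturns a result at 20% missing per arm?**
- Evaluable per therapist: 13 × 0.8 = 10.4. Design effect: 1 + 9.4 × 0.01 = 1.094.
- Effective number per arm: 104 / 1.094 = 95.06.
- Standard error: 29 × √(2 / 95.06) = 4.21. Critical difference: 1.96 × 4.206 = 8.24.
- Observed difference 10 (assumed): (10 − 8.24) / 0.20 = 8.8 points of one-arm shift.
- Observed difference 14.5 (the target): (14.5 − 8.24) / 0.20 = 31.3 points.

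**Step 5. Is bias below the gate like bias just above it?** For a 14.5-point one-arm departure, the bias is 14.5 × 0.21 = 3.05 points at 21% missing, 2.9 at 20% (95% of it), and 14.5 × 0.15 = 2.18 at 15% (71%).

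**The case against.** The plan is better than many: it prespecifies shifted multiple imputation, and the threshold was fixed in advance, so it cannot be tuned to the results. If dropout reaches the planned 30%, the analysis runs. If dropout is low, bias is smaller too. At 20% missing per arm, even a one-arm departure as large as the whole target effect moves the contrast by 2.9 points, less than its standard error of about 4.2. Analysis is by intention to treat, and the Outcomes section describes phone, email and text reminders and a replacement questionnaire without limiting them to patients still in therapy, so stopping sessions does not by itself make the outcome missing. All of this stands, and it limits the size of the problem. None of it makes the fraction missing a test of MAR.

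A reader might go further and infer that the plan applies one identical shift to both arms, so that its sensitivity analysis is empty. The document does not support that. It is silent on allocation by arm; several amounts, in both directions, are compatible with arm-specific shifts; and such detail may sit in a fuller document. Even a common shift cancels exactly only when missingness is equal: at 25% and 15% missing it moves the contrast by 1.45 points. Nor is it right that bias anywhere from 15% to 20% missing is nearly that at 21%: this is true at 20% but not at 15%.

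**Conclusion.** The point holds for the trigger. The article states a rule that makes its only departure-from-MAR analysis depend on the amount missing, and its own attrition expectations make it plausible that the analysis is never run. The consequence is modest. A target-size effect of 14.5 points would be secure against any but an extreme departure, with a tipping shift of about 31 points. A moderate result is less secure: an assumed 10-point difference would lose significance at a one-arm shift of about 8.8 points, at a level of missingness where the plan performs no check.

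These figures rest on the plan's SD of 29 and its own clustering allowance, equal allocation, 20% missing in each arm, a standard error that does not change with the shift, and illustrative values for the observed difference and the shifts. The question of shifts by arm is a matter for clarification; it is not an error in the stated text.

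**What to change.** Delete the 20% condition and state that the shifted multiple imputation will be run for the primary outcome whatever the amount missing. This also removes any need to define whether the 20% is counted per visit, per arm or overall.

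In the same sentence, state that the shifts will be varied separately by arm, including shifts in the Conquer Fear arm only, over a range such as 0 to 14.5 points or beyond, and that the shift at which the primary conclusion changes will be reported as a tipping point.

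The cost is a few more imputation runs and a short addition to the text. The sample size of 260 and the primary model are unaffected.
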